### Randomisation, blinding and informed consent

Women will be informed of the trial when induction of labour is planned or at the first visit to the labour ward in case of prelabour rupture of membranes. Subjects’ signed informed consent to participation will be obtained prior to randomisation and intervention (i.e. before any oxytocin stimulation).

Women will be randomised in a 1:1 ratio to either the continued oxytocin group or the discontinued oxytocin group using an Internet-based randomisation programme (Trialpartner). Random block-sizes of four will be used, and the women will be stratified by site, parity (nulliparous or parous +/− previous caesarean) and indication for oxytocin infusion (induction of labour or induction due to prelabour rupture of membranes (PROM)). The randomisation number generated by the computer programme corresponds to number of the studymedication (masked, identical ampoules). The personnel of the delivery ward will administer the medication according to existing guidelines concerning administration [5, 12, 13]. Women, caregivers, and trialmanagers will be blinded to the allocation due to the use of identical study medication preparations.

### Complications

In accordance with guidelines [5, 13] The infusion will be reduced or discontinued at any point of labour, if the following occur:
Tachysystole (> 5 contractions per 10 min, averaged over a 30-min window)Uterine contractions lasting 2 min or moreNon-reassuring CTG (recurrent variable decelerations, fetal tachycardia or bradycardia, minimal to absent baseline variability, late decelerations) or significant STAN event(s)Suspicion of uterine rupture

### Dystocia

If there is failure to progress, defined as less than two cm dilation over 4 h despite apparently adequate contractions, and/or maximal infusion rates (oxytocin or placebo), the study medication can be replaced with open-labelled oxytocin infusion.

If failure to progress persists, despite open-labelled oxytocin infusion for 4 h, caesarean section can be considered.

### Side effects and risks

We expect a rate of persistent failure to progress of 8–46% among the participants in the discontinued group versus 3–17% in the continued group [1–4]. Based on data from the pilot study [9], we expect a caesarean section rate of 15% in the discontinued group versus 22% in the continued group. According to the pilot study and previous studies [1–4], maternal and neonatal complications in the discontinued group are expected to be lower than in the continued group (The 2018 data for labour that are induced in Denmark indicate an acute caesarean section rate of 14.6%. However, the latter figure includes women who respond to prostaglandin alone and there are no data for women who require oxytocin infusion in addition).

All women will be monitored with continuous electronic fetal heart rate monitoring during labour to detect complications such as uterine tachysystole and non-reassuring/pathological fetal heart rate in accordance with national guidelines. Women and their newborns will be observed for at least 3–6 h postpartum (termination of study medication) according to the current practice on the delivery ward before discharged home.

Delivery ward staff is responsible for timely reporting of any adverse reactions to the trial manager.

Adverse reactions/events will be registered immediately in the electronic medical file of the patient. The Summary of Product Characteristics (SPC) of *Syntocinon®* will be used as reference [6] to determine whether a Serious Adverse Reaction is expected or unexpected. The primary investigator or a nominated deputy will go through the participants’ electronic medical record 7–30 days postpartum during data collection. The primary investigator will ensure that all relevant information about suspected serious unexpected adverse reactions that are fatal or life threatening is recorded. The primary investigator will report as soon as possible (and in any case no later than seven days) to the competent authorities concerned. The primary investigator will ensure that any relevant follow-up information is subsequently communicated within an additional eight days.

The primary investigator will report to the competent authorities concerned and to the Ethics Committees all other suspected unexpected serious adverse reactions as soon as possible but within a maximum of 15 days of first knowledge.

### Power calculation and statistical analysis

Based on the pilot study [9] we expect a caesarean section rate of 22% in the continued group. A clinically relevant relative reduction in the caesarean section rate would be 30%, corresponding to a caesarean section rate of 15% in the discontinued group. Aiming for a power (beta) of 80% and an alpha of 0.05, superiority can be shown with a sample size of 482 women in each group. Allowing for crossover and a dropout of 5% we aim to recruit a total of 600 women per treatment arm (1200 in total).

If superiority of oxytocin discontinuation vs. continued oxytocin stimulation for the reduction of the incidence of caesarean section cannot be shown, non-inferiority testing is a relevant alternative. It is plausible that improvements in secondary outcomes will be seen, even if there is no superiority on the primary outcome. To allow formal non-inferiority testing as an alternative, we define a post hoc non-inferiority boundary (margin, delta) at 1.09. This boundary is to exclude a rate of 22% in the continued oxytocin group as compared to 24% in the discontinued group.

Data will be analysed according the intention-to-treat principle. Basic demographic data will be presented with counts and percentages for categorical variables, mean and standard deviation for continuous Gaussian distributed variables, and median and interquartile range for continuous non-Gaussian variables. The primary outcome variable will be assessed by comparing the event rates in the two groups using a chi-square test with a significance threshold *p*-value of < 0.05. Results will be presented as absolute and relative risks along with 95% confidence intervals (Cl) and the numbers needed to treat (if applicable). Categorical secondary outcomes will be assessed in the same way as the primary outcome. For continuous secondary outcomes with a Gaussian distribution (following log transformation if appropriate) we will assess differences between groups using the student’s t-test, and with a non-parametric Mann-Whitney U test if the data are non-Gaussian. We will present time to delivery using Kaplan-Meier estimates and survival curves, and test the differences between the two groups using the log-rank test. We will use multivariate logistic regression with adjustment for indifferences in baseline characteristics to calculate odds ratios with 95% confidence intervals.

Subgroup analysis will be undertaken for the following subgroups:
Indication for stimulation (PROM and induction)Parity (nulliparous and parous)Previous caesarean section

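### The primary chi-square ignores the factors used to stratify randomisation; analysing by those factors is a free but modest gain in calibration and precision

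*Protocol article*

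**What the plan says.** **Design.** Under Randomisation, blinding and informed consent, allocation is 1:1, "Random block-sizes of four will be used", and "the women will be stratified by site, parity" and indication for oxytocin (induction, or induction because of prelabour rupture of membranes). Parous women are described as with or without a previous caesarean, which reads as three parity levels in all. The Abstract repeats these factors.

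**Analysis.** Under Power calculation and statistical analysis, the primary outcome is assessed by "comparing the event rates in the two groups using a chi-square test", at a threshold of 0.05. Absolute and relative risks with 95% confidence intervals follow. Neither the test nor the risks are said to be stratified or adjusted.

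**Other analyses in the same section.** A logistic regression adjusts for baseline differences and gives odds ratios. It is not the primary test and does not name the stratification factors. Indication, parity and previous caesarean appear otherwise only as subgroups.

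**The concern.** Blocking within strata nearly equalises the strata across the arms, so differences in caesarean rate between strata largely drop out of the treatment contrast. The plain chi-square and the crude intervals still count that variation in their variance. If the factors are prognostic, the estimated standard error exceeds the true one. The test then rejects less often than 5% under the null, and the intervals are wider than the design warrants.

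At stake is efficiency. The same interval would naturally serve the superiority result and the fallback reading against the 1.09 non-inferiority boundary.

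**Working it through.** **1. Reproduce the planned size.** The article says "we expect a caesarean section rate of 22% in the continued group", and a 30% relative reduction "corresponding to a caesarean section rate of 15% in the discontinued group", with 80% power and alpha 0.05 (sidedness not stated, two-sided assumed). With mean rate 0.185 and no continuity correction:

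n = [1.96·√(2·0.185·0.815) + 0.842·√(0.22·0.78 + 0.15·0.85)]² / 0.07² = 482 per group.

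This matches the article exactly, so the sample size was computed for the unadjusted test. The same formula gives 87.8% power at 600 per arm and 86.2% at 570 (after 5% dropout).

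**2. Type I error, parity split only.** The article gives no stratum-specific caesarean rates, so those below are assumptions that average 22%. The 55% nulliparous share follows from the Danish induction counts in the Background: 8065/(8065 + 6636) = 54.9%. With stratum weights w and rates p:

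ratio = Σ w·p(1−p) / (0.22·0.78); true type I error ≈ 2·[1 − Φ(1.96/√ratio)].

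| Nulliparous share | Rate, nulliparous | Rate, parous | Ratio | Type I error |
|---|---|---|---|---|
| 55% | 33% | 8.6% | 0.914 | 4.0% |
| 60% | 30% | 10.0% | 0.944 | 4.4% |
| 70% | 27% | 10.3% | 0.966 | 4.6% |

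**3. All factors, by simulation.** There were 20,000 replicates per scenario, with blocks of four within site × parity/previous caesarean × indication. Ten sites, the stratum shares and the stratum rates are assumptions. Monte Carlo error is about 0.2 points for power and 0.15 for type I error. Power is for 22% versus 15%. The second column gives control rates for nulliparous / parous / previous caesarean.

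| Prognostic strength | Control rates | Chi-square type I error, N=1200 | Power, chi-square → stratified, N=1200 | Power, chi-square → stratified, N=964 |
|---|---|---|---|---|
| None | 22 / 22 / 22% | 5.1% | 87.6 → 87.4% | 79.7 → 79.2% |
| Mild | 26 / 15 / 32% | 4.9% | 88.2 → 88.5% | 79.9 → 80.2% |
| Moderate | 28 / 10 / 39% | 4.4% | 88.2 → 89.2% | 81.3 → 82.0% |
| Strong | 30 / 5 / 54% | 3.9% | 89.4 → 91.2% | 81.4 → 83.9% |

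The 5.1% is simulation noise around 5%. The Cochran-Mantel-Haenszel test stays near 5% throughout. The true SD of the risk difference, divided by the unadjusted standard error, runs from about 1.00 (none) to 0.95 (strong). The crude interval is therefore about 0% to 5% too wide.

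**4. Convert power to women.** A rise in power from a to b is worth 1200·{[(1.96 + z_b)/(1.96 + z_a)]² − 1} women.

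- Parity-only simulations, 570 per arm: 0.868 → 0.875 gives (3.110/3.077)² − 1 ≈ 0.022, about 26 women; 0.872 → 0.887 gives about 59.
- Parity-only simulations, 482 per arm: 0.806 → 0.815 gives about 28; 0.812 → 0.832 gives (2.922/2.845)² − 1 ≈ 0.055, about 65.
- Strong scenario of step 3, the extreme of the assumed range: about 79 at N=1200 and about 85 per 1200 at the N=964 power levels.
- No prognostic value: zero.

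**5. Non-inferiority reading.** At 22% in both arms with 600 each, SE(log RR) = √(2·0.78/132) = 0.109. The upper 95% limit is exp(1.96·0.109) = 1.24. A 5% narrower interval gives 1.22. The largest observed risk ratio that would still exclude 1.09 moves from 1.09/1.24 ≈ 0.88 to 1.09/1.22 ≈ 0.89.

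**The case against.** The plan is internally consistent: the sample size was derived for the test that is named, and the target is exceeded. The article reports no caesarean rates by stratum. Its 55% nulliparous figure covers all Danish inductions, not oxytocin-treated women who reach the active phase. Site by three parity levels by two indications makes six cells per site, some of them sparse, and full stratification gains nothing if the factors are not prognostic. Adjusted and subgroup analyses are planned, and an analysis plan that is not shown might add a stratified test.

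Most of this stands and limits the size of the point. It does not remove the mismatch, because the article itself fixes the primary test as unadjusted. The logistic regression is secondary and gives odds ratios, whereas the boundary (24%/22% = 1.09) is a risk ratio. If its covariates follow observed imbalance, factors balanced by design are the ones likely to be left out. Subgroup analyses do not adjust the overall estimate.

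A reader might infer four stronger things, none of which is supported:

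- **That the test fails to control its 5% level.** The error falls below 5%, so false claims of superiority become no more likely.
- **That the trial is underpowered.** The planned 80% holds for the chi-square.
- **That about 50 to 110 women are wasted.** That figure is 1200 times the 4% to 9% variance reduction. It credits the analysis with a gain that stratified randomisation already gives the crude estimate. Only the estimated variance is too large.
- **That the non-inferiority result is materially damaged.** An upper limit of 1.24 or 1.22 is far above 1.09 either way.

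**Conclusion.** The mismatch between stratified randomisation and an unadjusted primary analysis is real. Its effect is a conservative test and slightly wide intervals, not an invalid inference. Under the assumed rates, type I error is about 3.9% to 5.0% at N=1200 and intervals are 0% to 5% too wide. The avoidable loss is zero to about 2 points of power at N=1200 (up to about 2.5 at N=964). In women, that is zero to about 65 per 1200 with a parity split only, and about 80 to 85 at the extreme of the assumed range for all factors. Every non-zero figure rests on stratum shares and rates that the documents do not give. This is a free improvement, not a threat to the trial's validity.

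**What to change.** Before unblinding, amend the primary analysis to one of these:

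- a Cochran-Mantel-Haenszel test stratified by the randomisation factors; or
- a model with treatment and those factors: site, parity/previous caesarean in three levels, and indication.

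Enter the factors as main effects, or pool sparse cells by a rule set in advance. Report the adjusted risk ratio and risk difference with 95% confidence intervals (Mantel-Haenszel, or marginal standardisation from the model). Use that risk-ratio interval for the 1.09 boundary. Keep the crude chi-square as a sensitivity analysis.

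The cost is a sentence or two in the protocol or analysis plan. No new data are needed, since the factors are recorded at randomisation, and the sample size need not change.

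### The supplementary logistic regression appears to choose its covariates by observed baseline imbalance and reports an odds ratio that is not directly comparable with the primary relative risk or the 1.09 margin

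*Protocol article*

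**What the plan says.** All of the analysis text is in the protocol article, section Power calculation and statistical analysis. The primary outcome, caesarean section, is compared between arms "using a chi-square test with a significance threshold" of 0.05. For effect size, "Results will be presented as absolute and relative risks along with 95% confidence intervals".

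For the fallback non-inferiority question, "we define a post hoc non-inferiority boundary (margin, delta) at 1.09", and the rates behind it follow: "This boundary is to exclude a rate of 22% in the continued oxytocin group as compared to 24% in the discontinued group".

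After the survival methods, the last sentence before the subgroup list brings in an adjusted model: "We will use multivariate logistic regression with adjustment for indifferences in baseline characteristics to calculate odds ratios with 95% confidence intervals". It names no covariates, no criterion for a difference, and no outcome to which the model applies.

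Under Randomisation, blinding and informed consent, "the women will be stratified by site, parity" (with previous caesarean among parous women) and indication for oxytocin, in blocks of four. Parity, previous caesarean and indication return as the subgroup factors.

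**The concern.** Read as differences, the sentence states a selection principle: a baseline variable enters the model because the arms happen to differ on it. Three things follow.

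- After randomisation the differences are chance. How far the arms differ on a variable does not show whether it predicts caesarean section, and prediction is what makes adjustment useful. With no candidate list or threshold, the model stays open until baseline data by arm have been seen.
- The principle works against the design. Factors used for stratification are kept in balance, so a rule that looks for imbalance passes over them. The primary chi-square ignores the strata, so this regression is the one described analysis in which they could enter as covariates.
- The model yields an odds ratio beside a primary result in absolute and relative risks and a margin that is a risk ratio. For an outcome near 20% the two scales differ visibly, and a covariate-adjusted odds ratio also changes with the covariates included.

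At stake are the credibility and usefulness of the adjusted estimate, not the primary test.

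**Working it through.** **Inputs from the article.** Control rate 22% ("we expect a caesarean section rate of 22% in the continued group"); target effect ("would be 30%, corresponding to a caesarean section rate of 15% in the discontinued group"); margin 1.09, from 24% vs 22%; alpha 0.05, power 80%, 482 per group needed, 600 per arm recruited, allocation 1:1. Two-sided testing is assumed.

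**1. The plan's own figure.** With pooled rate 0.185,

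n = [1.960·√(2·0.185·0.815) + 0.842·√(0.22·0.78 + 0.15·0.85)]² / 0.07² = (1.076 + 0.460)² / 0.0049 ≈ 482 per group.

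This matches the plan. The same formula gives 87.8% power at 600 per arm.

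**2. Scale.** OR = [p1/(1−p1)] / [p0/(1−p0)].

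- Margin rates: RR = 0.24/0.22 = 1.091; OR = (0.24/0.76)/(0.22/0.78) = 1.120. So 1.09 is a risk ratio.
- Target effect: RR = 0.15/0.22 = 0.682; OR = (0.15/0.85)/(0.22/0.78) = 0.626.
- RR 1.09 corresponds to OR 1.107 at a control rate of 14.6% (the article's figure for all induced labours in Denmark), 1.118 at 22%, and 1.134 at an assumed 30%.
- In reverse, OR 1.09 at 22% is RR 1.069. A crude upper odds-ratio limit between 1.09 and 1.118 would thus look as if it missed a margin that it meets.

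**3. How often chance alone selects something.** The article gives neither a number of candidates nor a threshold. Assuming k independent candidates screened at p<0.05, the chance of flagging at least one is 1 − 0.95^k: 23% for k = 5, 34% for 8, 40% for 10, 54% for 15, 64% for 20.

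**4. Why the strata are passed over.** With 1:1 blocks of four, the arms within a stratum can differ by at most two women at any time. Site, parity/previous caesarean and indication will therefore rarely look imbalanced.

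**5. Precision.** Simulation of 1200 women, 3000 runs per scenario, randomised within parity, control rate 22%. These assumptions are not in the article: 60% nulliparous; parity odds ratio 2, 4 or 8; eight other covariates, two of them weakly prognostic (odds ratio 1.35 per SD). The imbalance rule screened those eight at p<0.05. Parity was exactly balanced, so the rule could not pick it. The fixed set was parity plus the two prognostic covariates.

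| Parity OR | Power, unadjusted | Power, imbalance rule | Power, fixed set | Type I error, imbalance rule | SE of log RR, unadjusted → fixed set |
|---|---|---|---|---|---|
| 2 | 88.57% | 88.57% | 89.20% | 0.050 | 0.1221 → 0.1209 |
| 4 | 88.47% | 88.70% | 90.67% | 0.041 | 0.1194 → 0.1178 |
| 8 | 89.07% | 89.03% | 91.43% | 0.039 | 0.1202 → 0.1181 |

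- Imbalance rule minus unadjusted: 0.00, +0.23 and −0.04 points.
- Fixed set minus unadjusted: 0.63, 2.20 and 2.36 points, with the standard error of the log risk ratio 1 to 2% smaller.
- Covariate-adjusted odds ratio in these scenarios: 1.126 to 1.139 at 24% vs 22%, and 0.613 to 0.590 at 15% vs 22%. Both lie further from the risk ratio than the crude odds ratio does.
- The fixed-set model standardised to a risk ratio returns about 0.682 at the target effect and about 1.09 at the margin rates.

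**The case against.** The strongest reply is that nothing decisive rests on this sentence. The primary analysis is the chi-square test, with absolute and relative risks promised. The regression is not called primary and is not tied to the non-inferiority test. Adjusted odds ratios are a conventional supplement, and an article commonly leaves the covariate list to an analysis plan. The reading also depends on repairing a misprinted word. All of this limits the size of the point.

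It does not remove it. The article is not silent: it states a principle for adjustment and an effect measure, and both are poor choices. Taken literally, *indifferences* gives no usable rule, so the sentence needs correction on either reading.

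A reader might infer more than the document supports:

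- *That the rule inflates false positives.* The simulation shows type I error of 0.039 to 0.050.
- *That the odds ratio will be tested against 1.09.* The article never proposes this; the risk is of misreading when the figures are reported together.
- *That the odds ratio cannot be related to the risk ratio at all.* A crude one converts once a control rate is assumed. The adjusted one does not convert directly, because it also depends on the covariates.
- *That covariates are chosen after unblinding, by a p<0.05 screen, with the stratification factors barred.* The article states none of these. Judging imbalance does need baseline data split by arm, but timing and criterion are left open.

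**Conclusion.** The point holds as a weakness in a supplementary analysis and should be corrected. As stated, the rule adapts the covariates to chance, tends to leave out the factors on which the trial was stratified, and gives practically no precision in return. The loss is modest: roughly 0.6 to 2.4 points of power forgone. That figure rests on the assumed prognostic strengths and on a fixed set that contained the truly prognostic covariates; site, indication, dropout and crossover were not modelled. That the stratification factors predict caesarean section is likely but not quantified in the article. The scale mismatch needs no such assumption, since it follows from the article's own rates. The primary chi-square result and the sample size are unaffected.

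**What to change.** Replace the sentence with one stating that the adjusted analysis includes the randomisation factors (site, parity/previous caesarean, indication) and any further prognostic covariates named before unblinding, whatever the observed baseline balance. Report the adjusted risk ratio and risk difference with 95% confidence intervals, by marginal standardisation of the logistic model or by modified Poisson regression with robust variance. The odds ratio may be kept as an addition. State which outcomes the model covers.

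The cost is one sentence and no new data, since the randomisation factors are already recorded for every woman. Small sites may need pooling in the model, and the pooling rule should be fixed at the same time.

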### Monitoring

The trial is continuously monitored according to Good Clinical Practice (GCP). Each recruiting site is visited at least once per year by the external monitor who performs an audit on selective outcome measures.

An interim analysis is performed each year during the inclusion period. Three independent members have been assigned to the data monitoring committee (DMEC, see Additional file 2) and they have access to the results of the interim analysis. DMEC members safeguard the interests of trial participants, assess the safety of the intervention during the trial, and monitor the overall conduct of the clinical trial. No formal stopping rules have been made. A report is sent to the Trial Steering Committee (TSC, see Additional file 3) on the conclusion of the assessment made by the DMEC. The TSC provides independent advice to the trialists based on the DMEC conclusion.

The charter for the DMEC and/or the TSC can be obtained by contacting the corresponding author of the trial.

In case of important protocol changes, the amendment will be communicated to the relevant parties (site investigators, trial registry etc.).

